# STUDY ENPOINTS

## Primary Endpoints

- Safety (per CTCAE 5.0 criteria)

## Secondary Endpoints

- Disease control rate (DCR)
- Duration of response (DoR)
- Objective response rate(ORR per RECIST v1.1)
- Progression-Free Survival (PFS per RECIST v1.1)
- Overall surviral(OS))

# STUDY DESIGN

## Schematic Design

This study is a prospective, multi-cohort clinical trial designed to evaluate the safety and efficacy of chemotherapy(Etoposide + Carboplatin) in combination with the PD-1 antibody camrelizumab and the anti-angiogenic drug apatinib in the treatment of patients with extensive stage small cell lung cancer.

Study objectives: To explore the safety of induction chemotherapy followed by chemotherapy combined with immune and anti-angiogenic drugs for the first-line treatment of patients with ES-SCLC; (2) To explore the efficacy of induction chemotherapy followed by chemotherapy combined with immune and anti-angiogenic drugs for the first-line treatment of patients with ES-SCLC; (3) To explore the precision treatment population of patients with extensive small cell lung cancer treated with chemotherapy combined with immunological and anti-angiogenic agents after induction chemotherapy.

If subjects did not withdraw consent from the trial or were deemed by the investigator to be unsuitable for further trials, and each subject will be treated until disease progression or, drug-induced toxicities are intolerable, followed by a survival follow-up period.

[figure not shown]
(1) Etoposide: 100 mg/m2 IV Day 1-3; Carboplatin: AUC 5 mg/mL/min IV Day 1; Camrelizumab: 200 mg IV Day 1; Apatinib: 250 mg Po QD.

**Figure 1. Study Flow Chart**

# SAMPLE SIZE

The study plans to enroll 36 subjects.

# SUBJECT SELETION

## Inclusion Criteria

1. Pathologically confirmed extensive stage small cell lung cancer;
2. Extensive small cell lung cancer (per the Veterans Administration
3. Lung Study Group (VALG) staging system) not receiving systemic treatment;
4. Received prior surgery and adjuvant therapy for curative intent such as radiotherapy and chemotherapy; at least 6 months of treatment-free period since last chemotherapy, radiotherapy, or chemoradiotherapy to diagnosis of extensive-stage SCLC;
5. Measurable lesions according to Response Evaluation Criteria in Solid Tumors (RECIST) version 1.1;
6. Male or female ≥ 18 years of age and ≤ 75 years of age;
7. ECOG performance status score of 0-1;
8. Life expectancy ≥ 12 weeks;
9. Adequate organ system function (excluding the use of any blood components and cell growth factors during screening):
   1. Hemoglobin ≥ 9 g/dL
   2. Absolute neutrophil count ≥1.5×109/L
   3. Platelets ≥100 × 109/L
   4. Serum albumin ≥ 3/dL
   5. Total bilirubin ≤ ULN
   6. ALT and AST ≤ 1.5 × ULN; AKP ≤ 2.5 × ULN
   7. Serum creatinine ≤1.5 ULN or creatinine clearance(CrCl) ≥60 mL/min (Cockcroft -Gault formula). Negative urine protein or 24-hour urine protein quantification <1.0 g
   8. Thyroid stimulating hormone (TSH) ≤ULN (subjects with normal T3 and T4 levels are allowed to be enrolled although TSH＞ULN)
10. Contraception (e.g., IUD, contraceptives, or condoms); a negative pregnancy test within 7 days prior to enrollment for women of childbearing age;
11. Subjects voluntarily enrolled in this study and signed an informed consent form.

## Exclusion Criteria

1. Prior treatment with apatinib, anti-programmed cell death (PD)-1, anti-PD-1, or other immunotherapy against PD-1/PD- L1;
2. Carcinomatous meningitis, subjects with asymptomatic brain metastases and did not require immediate radiotherapy could be included in the study;
3. Other malignancies diagnosed and/or treated within 5 years prior to enrollment, except cured basal cell carcinoma of the skin and carcinoma in situ of the uterine cervix;
4. There are a variety of factors that affect the oral administration of medications, such as inability to swallow, posterior gastrointestinal resection, chronic diarrhea, intestinal obstruction, etc.;
5. Have an uncontrollable pleural effusion, pericardial effusion, or ascites that cannot be controlled by drainage or other procedures;
6. Subjects with spinal cord compression that has not been cured or resolved by surgery and/or radiotherapy, or patients with spinal cord compression diagnosed after treatment, who do not have clinical evidence of disease stabilization ≥1 week prior to enrollment;
7. Subjects with hypertension that is not well controlled with oral antihypertensive medication (systolic blood pressure > 140 mmHg, diastolic blood pressure >90 mmHg), with Grade I or greater myocardial ischemia or myocardial infarction, Grade I or greater arrhythmia (including QT interval ≥440 ms) or cardiac insufficiency;
8. Subjects with signs of bleeding or predisposition to bleeding, regardless of the degree of bleeding, within 2 months prior to the first dose; history of hemoptysis (defined as more than 2.5 ml of bright red blood) or unhealed wounds, ulcers, or fractures in the previous 2 weeks;
9. Incomplete recovery from adverse events due to prior therapy, except for alopecia which did not recover to grade ≤1;
10. Major surgery or significant traumatic injury within 28 days prior to enrollment;
11. An arterial or venous thromboembolic event within 6 months, such as transient ischemic attack, deep vein thrombosis, pulmonary embolism, and other cerebrovascular accidents;
12. Those with a history of substance abuse, inability to quit, or a mental disorder;
13. Suffering from a serious and/or uncontrollable illness;
14. Vaccination or attenuated vaccine within 4 weeks prior to the first injection;
15. Known allergy to the study drugs or excipients, history of severe allergic reaction to any monoclonal antibody; history of allergy to carboplatin or etoposide ;
16. Active autoimmune disease requiring systemic therapy within 2 years prior to first dose;
17. Immunosuppressive, systemic or local absorbable hormones (prednisone or other therapeutic hormones at doses > 10 mg/day) were administered to the patient. Immunosuppressive therapy was administered and continued for 2 weeks after the first dose;
18. Participation in a clinical trial of another anticancer drug within 4 weeks;
19. In the judgment of the investigator, there are other factors that may have led to the termination of the study.

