# TRETAMENT REGIMEN AND DOSAGE

1. **Induction treatment stage: chemotherapy induction 2 cycles, q3w**

- Etoposide: 100 mg/m2 IV Day 1-3;
- Carboplatin: AUC 5 mg/mL/min IV Day 1

1. **Combination treatment stage: chemotherapy + immunotherapy + antivascular therapy 2-4 cycles, q3w**

- Etoposide: 100 mg/m2 IV Day 1-3
- Carboplatin: AUC 5 mg/mL/min IV Day 1
- Camrelizumab: 200 mg IV Day 1
- Apatinib: 250 mg PO QD

1. **Maintenance treatment stage: immunotherapy + antivascular therapy, q3w**

- Camrelizumab: 200mg IV Day 1
- Apatinib: 250mg PO QD

The treatment was administered in 3-week cycles until PD, intolerable toxicity, death, patient withdrawal of information, or discontinuation in the evaluation of the investigator.

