**Table 3. Dose Adjustment Provisions for Apatinib**

| **NCI Toxicity Classification** | **Dose Adjustment for Hematologic Toxicity** |
| --- | --- |
| Grade 1, 2 Hematologic Toxicity | Maintain original dose level (appropriate symptomatic treatment) |
| Grade 3 Hematologic Toxicity | Firstly, suspend the drug and start symptomatic treatment, wait for the toxicity to recover to ≤ grade 2, then continue the treatment at the original dose |
| Grade 4 Hematologic Toxicity | Firstly, suspend the drug and start symptomatic treatment, wait for the toxicity to recover to ≤ grade 2, then continue the treatment at the original dose |
| **Dose Adjustment for Non-Hematologic Toxicity** | |
| Grade 1 Non-Hematological Toxicity | Maintain original dose level (appropriate symptomatic treatment) |
| Grade 2 Non-Hematological Toxicity | Symptomatic treatment, if the toxicity returns to ≤ grade 1 after two weeks, continue the drug; If the toxicity does not aggravated, suspend the drug and wait until the toxicity recovers to ≤ grade 1, continue to the original dose level. |
| Grade 3 Non-Hematological Toxicity | Suspend the drug and start symptomatic treatment, and continue treatment at the original dose when the toxicity recovers to ≤ grade 1; If grade 3 occurs again then discontinue related medication treatment. |
| Grade 4 Non-Hematological Toxicity | Suspend the drug and start symptomatic treatment, and continue treatment at the original dose when the toxicity recovers to ≤ grade 1. If it reccurs Grade 4 toxicity, terminate related drug therapy. (If life-threatening adverse events occur such as Grade4 renal damage, neurotoxicity, cardiotoxicity, hepatotoxicity, etc., terminate related drug therapy immediately) |
| Adverse reactions requiring special attention: In the event of hypertensive crisis, cerebral hemorrhage, ≥ Grade 2 pulmonary hemorrhage, ≥ Grade 3 other bleeding, arterial thrombosis, Grade 4 venous thrombosis, leukoencephalopathy syndrome, or gastrointestinal perforation, discontinue the administration of drugs associated with adverse effects and initiate prompt symptomatic treatment. | |

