**Non-hematologic toxicity**

Treatment should be delayed (up to 9 weeks) if any non-hematologic toxicity occurs until the value returns to baseline or below baseline (or Grade ≤ 1 if the subject has no toxicities at baseline). At the beginning of the subsequent cycles, the dose should be reduced based on the non-hematologic toxicity observed from the last cycle. Table 5 provides the dose modification recommendations for non-hematologic toxicity.

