## Screening Period

**The investigator will enroll subjects as follows.**

Obtain an ICF with the subject's signature prior to any study-related processes. Subjects were formally determined to be eligible for enrollment after review of the inclusion/exclusion criteria by the principal investigator or a designated person authorized by the principal investigator with appropriate training.

Subjects who do not meet the relevant criteria for this study (screening failure) may receive rescreen. Each subject may be rescreened once again. At the time of rescreening, the subject must re-sign the ICF and will be reassigned a subject identification number.

If a subject is discharged from the group or is ineligible for enrollment due to early onset of PD, withdrawal of ICF, or intolerance without 28 days of observation, the principal investigator of the group leader unit will decide whether or not to replenish the subject, as appropriate.

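### The bleeding, surgery and clot exclusions are judged only at screening and are not re-applied before the first apatinib dose, nominally six weeks into treatment

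*Protocol*

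**What the plan says.** - **Sequence.** Protocol Section 8 opens with "chemotherapy induction 2 cycles, q3w", consisting of etoposide and carboplatin only. Apatinib and camrelizumab join in the combination stage that follows. The Abstract lists all four agents as study drugs.
- **Eligibility review.** Section 11.1 states: "Subjects were formally determined to be eligible for enrollment after review of the inclusion/exclusion criteria by the principal investigator" or an authorized, trained designee. The Schedule of Activities and Table 7 mark the criteria only in the day -28 to -1 column. Table 8 (treatment visits) has no eligibility row.
- **Anchors in Section 5.2.** Item 8 bars "Subjects with signs of bleeding or predisposition to bleeding, regardless of the degree of bleeding, within 2 months prior to the first dose", and also hemoptysis above 2.5 ml or unhealed wounds, ulcers or fractures in the preceding two weeks, without naming the reference date. Item 10 reads "Major surgery or significant traumatic injury within 28 days prior to enrollment". Item 11 reads "An arterial or venous thromboembolic event within 6 months", with no reference date.
- **Rules during treatment.** Section 9.4 sets neutrophil and platelet minimums before each cycle. For other toxicity it says "Treatment should be delayed (up to 9 weeks) if any non-hematologic toxicity occurs until the value returns to baseline or below baseline", or to Grade 1 or lower if there was none at baseline. Section 9.3 and Table 3 govern apatinib. The Table 3 row on events needing special attention names, among others, "≥ Grade 2 pulmonary hemorrhage, ≥ Grade 3 other bleeding, arterial thrombosis, Grade 4 venous thrombosis", with the action "discontinue the administration of drugs associated with adverse effects and initiate prompt symptomatic treatment".

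**The concern.** Section 1 (Background) explains the concern behind the design. Small-cell tumors often invade large vessels, this may raise the bleeding risk under anti-vascular therapy, and a preceding intervention might lower it. The exclusions for bleeding, unhealed wounds, surgery and clots bear on that hazard, but they look back from the start of chemotherapy or from enrollment. The hazard begins when apatinib starts.

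A bleed, clot or operation during induction falls after the last date on which these criteria are judged. Two investigators could then handle the same subject differently and both comply. The stake is mainly patient safety, in a trial whose primary endpoint is safety (Section 2.1).

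**Working it through.** **1. Timing.** Inputs: two induction cycles of 21 days (Section 8); review on day -28 to -1 (Schedule of Activities). The protocol states no figure for the gap, so there is none to reproduce.

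- First apatinib dose: 1 + 2 × 21 = day 43.
- With no day 0, day -k lies k days before day 1, so the gap is k + 42. For k = 1 it is 43 days; for k = 28 it is 70 days.
- The visit window of ±3 days widens this to 40 to 73 days.
- The Schedule's medication row can be read as one to two induction cycles. With one cycle the gap is k + 21, or 22 to 49 days.
- Table 8 prints apatinib across all cycle columns but refers back to Section 8, so Section 8 is followed here.

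**2. What existing rules do with an event during induction.**

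| Status at cycle 3 day 1 | Section 9.4 | Table 3 | Result |
|---|---|---|---|
| Bleeding or hemoptysis, Grade 1 or resolved | Passes: Grade 1 or lower, or back to baseline | Ordinary rows keep the dose at Grade 1 and allow it after recovery; Grade 1 is below the special-row floors for pulmonary and other bleeding | No rule on starting apatinib, although item 8 bars bleeding of any degree at entry |
| Venous thrombosis below Grade 4, settled | Passes once Grade 1 or lower | Below the special-row floor; ordinary rows allow treatment after recovery | No rule on starting apatinib, although item 11 bars it at entry |
| Major surgery in the preceding 28 days | Concerns toxicity, not an interval after surgery | Not mentioned | No interval before apatinib, although item 10 sets 28 days at entry |

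Table 3 adjusts, suspends or stops apatinib. Section 9.2 covers interruptions for unrelated medical, surgical or accidental events and asks for resumption within two weeks unless the investigator decides otherwise. That is shorter than item 10's 28 days, and it concerns resuming treatment, not starting a new drug.

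**3. Which windows can be hard rules at cycle 3 day 1.** Take two months as 61 days and six months as 183 days.

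- Hemoptysis on day 42: 42 + 14 = day 56, which is 13 days after day 43.
- Surgery on day 42: 42 + 28 = day 70, which is 27 days after day 43. Each date moves by one day if the last day of the window counts as inside it.
- Any bleeding on days 1 to 42: 1 + 61 = day 62 to 42 + 61 = day 103, a delay of 19 to 60 days.
- Thromboembolism on days 1 to 42: 1 + 183 = day 184 to 42 + 183 = day 225. Cycle 6, the last possible combination cycle, ends on day 6 × 21 = 126.

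The two- and four-week windows are workable as delays. A hard two-month or six-month window would withhold apatinib for much or all of the combination stage, so those events suit a recorded decision better.

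**The case against.** The strongest case against is that the protocol is far from silent:

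- Platelets must reach 100,000/μL before each cycle, the same limit as at entry, and coagulation and stool tests recur.
- Blood pressure is measured before each camrelizumab dose, and ECG and vital signs recur by cycle. Item 7 (hypertension and cardiac status) is therefore measured at the right time.
- Table 3's ordinary rows suspend apatinib for Grade 3 or 4 non-hematologic toxicity, and for Grade 2 that has not settled.
- Section 13.6 excludes procedures from adverse-event reporting, but it then requires the condition behind an operation to be reported if it qualifies, with the operation documented as treatment.
- Sections 9.1, 9.2 and 13.4 require reasons for delays and the management of adverse events to be recorded.

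All of this stands. A reader might infer that a subject can start apatinib after such an event with no rule at all and nothing on record. The documents do not support that: part of the ground is covered, and delays and adverse events are recorded. What they lack is a rule, or a required decision, on starting apatinib in the three situations tabulated.

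The action in Table 3's special row can be read in two ways. It may mean drugs that caused the event, which cannot include apatinib before its first dose, or drugs known to cause such events, which could. Even the second reading leaves lesser bleeding and venous clots below the grade floors.

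Entry limits are also commonly stricter than on-treatment limits, and Table 3 keeps the apatinib dose at Grade 1. That argues for a recorded decision instead of a blanket ban. It does not answer the point, because Table 3 adjusts a drug already being taken, whereas cycle 3 day 1 is a first exposure. Finally, Figure 1 and Annex VI are not shown. Section 9.2 describes Annex VI as camrelizumab guidance, but a start condition in Figure 1 cannot be excluded.

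**Conclusion.** The concern holds in limited form. Items 8, 10 and 11 are reviewed only at screening, nominally 43 to 70 days before the first apatinib dose, or 22 to 49 days with one induction cycle. No text shown applies them, or a substitute, when that drug starts. The uncovered cases are Grade 1 or resolved bleeding or hemoptysis, a settled venous thrombosis below Grade 4, and recent major surgery during induction. Item 7 is secondary: it lacks a starting limit, not a measurement.

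A reader might take the size of the problem from the fact that any bleed or clot during the 42 induction days would fall inside a two- or six-month look-back. That only compares window lengths with the length of induction and says nothing about risk. The protocol gives no event rate, so no number of affected subjects is claimed. One subject would be 1/36 = 2.8 percentage points of any rate over the planned 36.

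The conclusion assumes that Section 8 governs the sequence, that the first dose in item 8 means chemotherapy, and that Figure 1 holds no start condition. It is a cheap improvement to patient safety and does not invalidate the analysis. Adverse events are collected from consent, so most such subjects could be traced afterwards.

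**What to change.** Anchor items 8, 10 and 11 to the first apatinib dose as well as to study entry. Add a check on cycle 3 day 1, completed before that dose, drawing on adverse-event, concomitant-treatment, vital-sign, ECG and coagulation data already scheduled:

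- **Hemoptysis above 2.5 ml or an unhealed wound within two weeks, or major surgery within 28 days:** delay apatinib until the window clears.
- **Any other bleeding, or any thromboembolic event, during induction:** record a decision to start, delay or omit apatinib, with the reason.
- **Blood pressure and QT:** state the limits for starting apatinib; item 7's entry values (140/90 mmHg, 440 ms) are the obvious candidates.

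Chemotherapy and camrelizumab continue under their own rules. Report how many subjects met an item and whether they started apatinib.

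The cost is protocol wording and one checklist on the cycle 3 case report form page, with no added procedure. The downside is that a few subjects would start apatinib late or not at all.

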# WITHDRAWAL CRITERIA

- Subjects withdrew informed consent.
- Progression of the disease on imaging.
- Those who cannot tolerate toxicity.
- Subjects missed visits or had positive blood HCG;
- Other situations where the investigator felt it necessary to withdraw from the study.

# TERMINATION CRITERIA

- Unintended or unacceptable risks to the subject are identified;
- The study drug/trial treatment is ineffective, or it is pointless to continue the trial;
- For reasons such as difficulties in subject enrollment or frequent protocol deviations, the declarant decided to terminate the study.

# TRETAMENT REGIMEN AND DOSAGE

1. **Induction treatment stage: chemotherapy induction 2 cycles, q3w**

- Etoposide: 100 mg/m2 IV Day 1-3;
- Carboplatin: AUC 5 mg/mL/min IV Day 1

1. **Combination treatment stage: chemotherapy + immunotherapy + antivascular therapy 2-4 cycles, q3w**

- Etoposide: 100 mg/m2 IV Day 1-3
- Carboplatin: AUC 5 mg/mL/min IV Day 1
- Camrelizumab: 200 mg IV Day 1
- Apatinib: 250 mg PO QD

1. **Maintenance treatment stage: immunotherapy + antivascular therapy, q3w**

- Camrelizumab: 200mg IV Day 1
- Apatinib: 250mg PO QD

The treatment was administered in 3-week cycles until PD, intolerable toxicity, death, patient withdrawal of information, or discontinuation in the evaluation of the investigator.

# DOSE AJUSTMENT AND DISCONTINUATION OF ADMINISTRATION

## General Rules for Dose Adjustment

- Reasons for dose adjustments or delays in administration, measures taken, and results should be documented in the subject's medical record and electronic case report form (CRF).
- If concomitant symptoms were present at baseline, it was the investigator to decide whether the dose would be adjusted according to the level of change in the adverse effect. For example, a subject with a Grade 1 "weakness" status at baseline and a Grade 2 "weakness" status during the study treatment period may be considered a "weakness" condition. The dose should be adjusted for grade 1 toxicity.
- In the event that several adverse reactions of different grades or severity occur simultaneously, dose adjustments will be based on the highest grade observed.
- If a dose adjustment is required solely due to an abnormal laboratory hematology test, the dose will be adjusted based on the hematology test prior to the start of the treatment cycle.
- The current dose will be continued without dose adjustment or suspension of treatment when, in the evaluation of the investigator, the adverse reaction is unlikely to progress further to a serious or life-threatening event.
- If the toxicity is caused by another medication, no dosage adjustment of the other medication is necessary.
- Permanent discontinuation of one therapeutic agent prior to the onset of PD will not affect the continued use of other therapeutic agents.
- If one of the therapeutic medications is suspended due to an adverse reaction, but not all of the medications, the treatment is still counted as one treatment cycle.

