## Apatinib Dose Adjustment

The initial dosage of apatinib is 250mg once daily (250mg qd). If intolerable adverse effects occur, the dosage can be adjusted to 250mg every other day (250mg qod). If intolerance persists, discontinue the medication until symptoms reduce to Grade 1 or lower, then resume at 250mg qd. Permanent discontinuation is recommended if Grade 3 or higher adverse effects recur.

During treatment, suspension of administration is required for reasons of non-recovered drug toxicity, and the cumulative duration of dosing suspension should not exceed 2 weeks per dosing cycle to ensure that the subject receives the drug strength of the treatment. If the investigator determines that an adverse reaction is caused by apatinib, apatinib dosing may be suspended without affecting the use of other medications. Refer to Table 3 for apatinib dose adjustment.

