**Table 5. Dose Modification or Treatment Discontinuation due to Non-Hematologic Toxicity**

| **Toxicity** | **Modified Carboplatin Dose (by % of Previous Dose)**^a^ | |
| --- | --- | --- |
| Diarrhea | Grade 3 or 4^b^ | 75% |
| Nausea/Vomiting^C^ | Grade 3 or 4 | 75% |
| Neurotoxicity | Grade 2 | 75% |
| Grade 3 or 4 | 50% or permanent discontinuation |  |
| AST, ALT, or Bilirubin  Increased | Grade 3 | 75% |
| Grade 4 | Discontinuation |  |
| Others | Grade 3 or 4 | 75% |

a The carboplatin dose can be modified by a specific percentage of the original AUC if deemed appropriate by the investigator. Previous dose: The calculated dose before dose administration of each cycle.
b Antidiarrheal agents are used for Grade 3-4 diarrhea or for any grade of diarrhea that requires hospitalization.
c Even when antiemetic therapy has been given.

Diarrhea should be treated with appropriate antidiarrheal agents. Nausea and/or vomiting should be treated with appropriate anti-emetics. If Grade 3 or 4 nausea/vomiting occurs, anti-emetics should be used and the dose should be reduced by 25% in the next cycle. The original dose should be resumed as soon as the subject is able to tolerate. If Grade 3 or 4 neurotoxicity occurs,chemotherapy should continue at 50% of the previous dose after improvement, or immediately be discontinued (based on the investigator's judgment).

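### Section 9.1 lets the highest grade decide the dose when reactions coincide, but for carboplatin (clearly) and apatinib (secondarily) the lower-grade reaction can carry the stricter action

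*Protocol*

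**What the plan says.** Section 9.1 (General Rules for Dose Adjustment) states: "In the event that several adverse reactions of different grades or severity occur simultaneously, dose adjustments will be based on the highest grade observed". It names no exception, and no clause says whether the drug-specific sections prevail over it. Section 9.1 also provides that a drug is not adjusted for a toxicity caused by another drug, so the rule matters when both reactions are attributed to the same drug.

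**Carboplatin (section 9.4, Table 5).** Grade 3 or 4 neurotoxicity is assigned "50% or permanent discontinuation". Grade 3 or 4 diarrhea, nausea/vomiting and other toxicity are each assigned 75% of the previous dose. The text under the table repeats the neurotoxicity instruction without reference to other events: "chemotherapy should continue at 50% of the previous dose after improvement, or immediately be discontinued", at the investigator's judgment.

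**Apatinib (section 9.3, Table 3).** For Grade 3 non-hematologic toxicity: "If grade 3 occurs again then discontinue related medication treatment". For Grade 4 hematologic toxicity: "wait for the toxicity to recover to ≤ grade 2, then continue the treatment at the original dose". For Grade 4 non-hematologic toxicity: "continue treatment at the original dose when the toxicity recovers to ≤ grade 1. If it reccurs Grade 4 toxicity, terminate related drug therapy", with immediate termination if life-threatening. The section 9.3 text adds: "Permanent discontinuation is recommended if Grade 3 or higher adverse effects recur".

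Section 9.4 has one combination rule of its own. When both the neutrophil and the platelet count call for a change, the lower dose is given.

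**The concern.** Section 9.1 chooses which reaction governs by its grade number. That protects the subject only if, within one drug, strictness of action never falls as grade rises. Where it does fall, adding a more severe second toxicity moves the subject from a stricter instruction to a milder one. An investigator following section 9.1 to the letter could then give carboplatin at 75%, or plan to resume apatinib at full dose, when one of the two toxicities alone would have meant half the dose or stopping.

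Tables 3 and 5 say what to do for each toxicity but not how to combine two. For the combinations below, section 9.1 is the only written combination rule, so two sites acting in good faith could treat the same subject differently.

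**Working it through.** No sample-size or error-rate figure is involved, and the plan states no number to reproduce. The check sets the rows side by side and asks whether, for two reactions attributed to the same drug, the lower-grade one ever has the stricter action.

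**Carboplatin (Table 5).** Lower-grade reaction: Grade 3 neurotoxicity, which alone means 50% or stop.

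| Coinciding Grade 4 reaction | Its own action | Section 9.1 points to | Stricter of the two |
| --- | --- | --- | --- |
| Diarrhea | 75% | 75% | 50% or stop |
| Nausea/vomiting | 75% | 75% | 50% or stop |
| Other toxicity | 75% | 75% | 50% or stop |
| AST, ALT or bilirubin | discontinue | discontinue | discontinue (no conflict) |

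Grade 2 neurotoxicity (75%) gives no conflict, because every Grade 3 or 4 row is 75% or stricter.

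Size of the gap: 0.75 / 0.50 = 1.5. For a first reduction from AUC 5, 5 × 0.75 = 3.75 against 5 × 0.50 = 2.5, a difference of 1.25 AUC units. If the investigator would have stopped carboplatin, the gap is the whole 3.75.

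**Apatinib (Table 3, ordinary graded rows).** Lower-grade reaction: recurrent Grade 3 non-hematologic toxicity, which alone means discontinuation.

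| Coinciding Grade 4 reaction | Its own action | Section 9.1 points to | Stricter of the two |
| --- | --- | --- | --- |
| Hematologic | suspend, then original dose | suspend, then original dose | discontinue |
| Non-hematologic, first, not life-threatening | suspend, then original dose | suspend, then original dose | discontinue |
| Non-hematologic, recurrent or life-threatening | terminate | terminate | same (no conflict) |

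Here the section 9.3 text still recommends permanent discontinuation, because a Grade 3 effect has recurred. The document therefore contains the stricter answer as well as the milder one.

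**Camrelizumab (Table 1).** No conflict. Every Grade 2 entry is suspension and every Grade 4 entry is permanent discontinuation, so a lower grade is never stricter. This sets aside note c, which leaves Grade 4 laboratory abnormalities to clinical evaluation.

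**Consistency with section 9.4.** The neutrophil-plus-platelet rule takes the lower dose. Applied to the combinations above, the same principle gives the last column of each table, not the section 9.1 column.

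**The case against.** The strongest reply is that section 9.1 is headed as general and the drug-specific provisions follow it, so a sensible investigator would let the specific text govern. The instruction under Table 5 for Grade 3 or 4 neurotoxicity is unconditional, and a highest-grade rule is hardly meant to relax a dose because a worse toxicity has been added. This carries weight as to what was probably intended. It does not remove the conflict, because the protocol never says that specific provisions prevail, and the tables do not say how to combine two toxicities.

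Three further objections stand in part.

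- **Table 5 is advisory.** Section 9.4 describes its scheme as a guideline and Table 5 as recommendations, and leaves the choice between 50% and stopping to the investigator. A reader might infer that section 9.1 forces the milder carboplatin dose; the document does not support that.
- **The apatinib case is weaker.** It depends on recurrence, which is a matter of history rather than grade, and the section 9.3 text still recommends stopping. That text also disagrees with the hematologic rows of Table 3, which resume the original dose with no stop on recurrence. That mismatch arises with a single toxicity, is a separate point, and is not cured by rewriting section 9.1.
- **No proportion of affected combinations is meaningful.** The tables above show three carboplatin and two apatinib combinations. With finer splitting of Table 3, such as counting differences in the recovery threshold, the five become 6, 7 or 8. The counts describe the tables, not risk.

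A reader might also infer that section 9.1 could displace the special-attention row of Table 3 (bleeding, thrombosis, perforation and similar events). That row tells investigators to "discontinue the administration of drugs associated with adverse effects and initiate prompt symptomatic treatment" without condition and partly without grade. It is most naturally an override, so it is not part of this point.

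**Conclusion.** The point holds as a minor safety correction. Read literally, section 9.1 gives a milder answer than the drug-specific text for Grade 3 neurotoxicity with Grade 4 diarrhea, nausea/vomiting or other toxicity under carboplatin (75% against 50% or stop). Less strongly, it does so for recurrent Grade 3 non-hematologic toxicity with a Grade 4 hematologic event, or with a first non-life-threatening Grade 4 non-hematologic event, under apatinib.

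This rests on two assumptions: both reactions are attributed to the same drug, and section 9.1 is applied as written. The combinations are taken to be uncommon, since each needs two high-grade reactions at once. The protocol gives no event rates, so no number of the 36 planned subjects is claimed.

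Because safety is the primary endpoint, a reader might infer that the endpoint is compromised. The document does not support that: adverse events are graded and recorded whichever dose action follows, so its definition and recording are unaffected.

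**What to change.** Replace the sentence in section 9.1 with: *When several reactions attributed to a drug occur simultaneously, determine for each reaction the action its drug-specific provision assigns to that reaction alone, and apply the most restrictive of these; special-attention events in Table 3 always take precedence.*

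This resolves all the combinations above and extends the lower-dose principle that section 9.4 already uses for neutrophils and platelets. The sentence should not be broadened to the strictest statement found anywhere in a drug's text or table. That would turn the section 9.3 recommendation into a mandatory stop: a second Grade 3 hematologic event, which Table 3 alone would let resume, would end apatinib whenever any minor reaction coincided. The mismatch between the section 9.3 text and the hematologic rows of Table 3 should be settled separately.

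The cost is one sentence by protocol amendment, with no added data, visits or subjects. The downside is slightly more dose reductions or stops in rare combined-toxicity cases.
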